# Impact of motivational feedback on levels of physical activity and quality of life by activity monitoring following knee arthroplasty surgery—protocol for a randomized controlled trial nested in a prospective cohort (Knee-Activity)

**DOI:** 10.1186/s12891-024-07878-0

**Published:** 2024-10-02

**Keywords:** Knee arthroplasty surgery, Knee osteoarthritis, Motivational feedback, App, RCT

## Abstract

**Background:**

Evidence on how to improve daily physical activity (PA) levels following total knee arthroplasty (TKA) or medial uni-compartmental knee arthroplasty (mUKA) by motivational feedback is lacking. Moreover, it is unknown whether a focus on increased PA after discharge from the hospital improves rehabilitation, physical function, and quality of life. The aim of this randomized controlled trial (RCT) nested in a prospective cohort is (a) to investigate whether PA, physical function, and quality of life following knee replacement can be increased using an activity monitoring device including motivational feedback via a patient app in comparison with activity monitoring without feedback (care-as-usual), and (b) to investigate the potential predictive value of PA level prior to knee replacement for the length of stay, return to work, and quality of life.

**Methods:**

The study is designed as a multicenter, parallel-group, superiority RCT with balanced randomization (1:1) and blinded outcome assessments. One hundred and fifty patients scheduled for knee replacement (TKA or mUKA) will be recruited through Odense University Hospital, Denmark, Vejle Hospital, Denmark and Herlev/Gentofte Sygehus, Denmark. Patients will be randomized to either 12 weeks of activity monitoring and motivational feedback via a patient app by gamification or 'care-as-usual,' including activity monitoring without motivational feedback. The primary outcome is the between-group change score from baseline to 12-week follow-up of cumulative daily accelerometer counts, which is a valid proxy for average objectively assessed daily PA.

**Discussion:**

Improving PA through motivational feedback following knee replacement surgery might improve post-surgical function, health-related quality of life, and participation in everyday life.

**Trial registration:**

ClinicalTrials.gov, ID: NCT06005623. Registered on 2023–08-22.

**Trial status:**

Recruiting.

**Supplementary Information:**

The online version contains supplementary material available at 10.1186/s12891-024-07878-0.

## Background

### Burden of disease

Musculoskeletal disorders, including knee osteoarthritis (OA), result in decreased physical activity (PA), leading to an increased incidence of chronic diseases [1]. Moreover, knee OA leads to work-related inactivity, a vicious downward spiral of increased symptoms, and a marked decrease in quality of life [2, 3]. The lifetime risk of developing symptomatic knee OA is estimated to be 45% [4].

### Total- or uni-compartmental knee arthroplasty and patient satisfaction

Knee replacement surgery by total knee arthroplasty (TKA) and medial uni-compartmental knee arthroplasty (mUKA) are two of the most frequently performed procedures in orthopedic surgery [5], and the lifetime risk of undergoing knee replacement if one suffers from OA is 30% [6]. Worldwide, over a million patients receive knee replacement surgery each year, and the numbers are expected to increase further due to the growing elderly population [7].

Despite successful surgical procedures, knee replacement patients still demonstrate decreased function and PA level, earlier retirement, less income, increased cost for health and home care compared to matched controls [8, 9]. Moreover, nationwide data underline the need for optimized treatment and/or rehabilitation as 20% of patients are dissatisfied one-year post-surgery, and poor postoperative knee function is negatively associated with patient satisfaction [10].

### Physical activity

Early mobilization on the day of surgery and a short length of hospital stay (median one day) have been achieved using the so-called fast-track protocols for knee replacement [11, 12]. However, little is known about the actual PA level and return to active daily living of the patients after discharge and in the early rehabilitation phase. Studies suggest that higher levels of PA before surgery can lead to better postoperative outcomes, including faster recovery and improved functional capacity [13, 14]. However, more evidence is needed to fully understand this relationship.

Low levels of PA have consequences such as increased all-cause mortality and chronic comorbidity [15]. This is also evident for knee OA patients [16]. On the contrary, regular PA at moderate or high intensity is associated with substantial health benefits [17]. Thus, evidence on improving PA with the perspective of a better post-knee replacement outcome is needed.

Only a few studies have objectively evaluated PA levels in OA patients, and thus, the influence of optimizing PA following knee replacement still needs to be answered. In a Dutch study, De Groot et al. (2007) observed that PA levels of patients with end-stage OA of the hip and knee were reduced (11%) compared to matched healthy controls [18]. Reduced PA was also found in Swedish patients scheduled for TKA compared to a healthy population [19]. In addition, it was shown that age and body mass index (BMI) were negatively associated with PA levels, indicating that specific interventions to improve PA, especially for heavier and older OA patients, are needed. Recently, a Danish study on fast-track TKA observed that PA levels were significantly reduced three weeks following TKA compared to preoperatively, calling for early stratified physiotherapeutic interventions [9]. The overall post-surgical improvement in physical activity for knee replacement patients has been questioned. Holsgaard-Larsen and Roos (2012) [18] found that PA levels remained low after surgery. Similarly, Kahn and Schwarzkopf (2016) [19] concluded that post-surgery activity levels were not significantly higher than pre-surgery levels. Furthermore, Hodges et al. (2018) [20] concluded that PA levels improved after TKA, but 12 months after surgery, about half of the patients did not meet the World Health Organization's recommendation for activity. This calls for improved and perhaps also individually stratified rehabilitation strategies in patients at risk for reduced postoperative PA and function [21].

### Health technology

Health technology, such as wearables and motivational feedback using gamification and nudging principles, are new features within health science. Gamification is traditionally defined as using game mechanics in non-gaming contexts to engage audiences [18] while nudging is a subtle and non-coercive method to influence decisions and behaviors for individual or societal benefit [22]. The use of smartphone apps and wearable devices in monitoring patients’ recovery are on the rise. Constantinescu et al. (2022) [23], in a systematic review, emphasized the potential of the technology to improve rehabilitation and increased self-engagement in TKA patients. However, the review concluded that more research is needed to fully understand the long-term effects and maximise the potential of these technologies. This highlights the need for further exploration into how motivational feedback, through nudging and gamification strategies, can be integrated to sustain physical activity and optimize health outcomes. Incorporating wearables and principles of motivational feedback such as gamification and nudging into health science could catalyze an individualized approach focused on increasing patient motivation for PA with expected improved physical functioning, faster and safer return to work, and increased quality of life. Thus, integrating individual rehabilitation goals into wearables may prioritize a more personalized approach and, thereby, potentially improve the effectiveness of rehabilitation following knee replacement surgery. The use of gamification and nudging has been shown to increase PA in overweight and obese adults [24]. Furthermore, a recent RCT study from Van der Walt et al. (2018) [25], on TKA and THA patients has shown that feedback, only on step counts per day, can play a crucial role in motivating patients to increase their daily PA.

SENS motion® (SENS Innovation ApS, Copenhagen, Denmark [26]) is a wireless medical accelerometer for collecting objective data on PA from large cohorts of patients. SENS motion® has developed a patient app with motivational feedback (Appendix 1, Fig. 3; App interface). The app has shown that hospitalized elderly patients with heart and lung diseases were motivated to be physically active for 51 min more each day [27]. The SENS system’s ability to monitor PA has been validated on knee-OA patients [28] and thus, the patient app with motivational feedback may provide a clinically relevant impact on patient self-mobilisation following discharge from knee replacement surgery.

## Objectives of the studies

This multi-center randomized controlled trial (RCT) nested in a prospective cohort aims to investigate whether PA following knee replacement surgery (TKA or mUKA) can be optimized using an activity monitoring device, including motivational feedback, compared with activity monitoring without feedback (care-as-usual). Furthermore, a prospective cohort will investigate the predictive value of PA level prior to knee replacement for the post-surgical length of stay, return to work, and quality of life.

### Hypotheses

#### RCT study

Using an activity monitoring device the first 12 weeks after discharge, including visual and motivational feedback on PA, shows a superior effect on increased PA (primary outcome), steps per day, minutes of PA, self-reported PA, self-reported function and pain, quality of life, global perceived effect on patient experience with knee problems, and return to work (secondary outcome measures) compared to no motivational feedback from the activity monitor, defined as 'care as usual', in knee replacement patients.

#### Prospective cohort

PA prior to knee replacement is a predictive measure for length of hospital stay, post-surgical function, quality of life, and return to work.

## Methods/Design

### Patient involvement

The current hypotheses have been discussed with our local patient panel, and it has raised various considerations about how the patient app should provide motivational feedback. These considerations include the choice between using a smartphone or a tablet, the delivery of feedback through notifications or on request, and whether the feedback should align with official PA guidelines or be customized to the individual's progress.

Subsequently, qualitative interviews were conducted with patients (*n* = 10) who had tested the app for one month with the aim of providing input for improvements of a prototype of the patient app. Feedback from these interviews suggested minor improvements that were implemented in an updated patient-specific app version before the inclusion of the first patient.

### Study design

The RCT is a multicenter randomized (1:1) parallel-group superiority trial with a blinded statistical analysis toward group allocation (level of evidence: II) nested in a longitudinal prospective cohort study. The cohort study includes patients unwilling to participate in the RCT study. The study protocol adheres to the SPIRIT Statement (Standard Protocol Items: Recommendations for Interventional Trails) (see Additional file 1 for the SPIRIT Checklist and Fig. 1 for the SPIRIT Figure). The reporting of the RCT study will follow the CONSORT Statement (Consolidated Standards of Reporting Trials) [29], while the cohort study will be reported in accordance with the STROBE statement [30].

**Fig. 1 Fig1:**
[figure not shown]
SPIRIT Figure. Template of content for the schedule of enrollment, interventions, and assessments. Abbreviations: PA: Physical activity; PROM: Patient-reported outcome measures; IPAQ: The International Physical Activity Questionnaire; OKS: Oxford Knee Score; EQ-5D-5L: Health-related quality of life; GPE: Global Perceived Effect

### Participants, randomization, and blinding

#### Participants and settings

Patients will be recruited from the Department of Orthopedics and Traumatology, Odense University Hospital, Denmark, and the Department of Orthopedic Surgery, Lillebaelt Hospital, Vejle, Denmark. Prior to inclusion, eligible patients (Table 1; Inclusion and exclusion criteria), will receive verbal and written information about the conditions of the trial and sign a standardized consent form. The longitudinally prospective cohort study includes patients unwilling to participate in the RCT study.

**Table 1 Tab1:** Inclusion and exclusion criteria for patients in the study

Inclusion	Exclusion
Age: 40–85 years	Difficulty adhering to the study protocol
Patients scheduled for primary TKA/mUKA	Refusal of standard care
Understanding both verbal and written Danish language	Known- or newly diagnosed malignancy or palliative care
	Participation in an interventional clinical trial during the last 3 months potentially interacts with the aims of the current study
	Do not own a smartphone
	Undergone surgery using robot-assisted technology (CAS)

*Abbreviations**: **TKA* Total knee arthroplasty, *mUKA* Medial uni-compartmental knee arthroplasty

#### Randomization

Randomization is performed internet-based using REDCap Randomize, allocated 1:1. Randomization occurs after baseline measurements on the day of surgery. The randomization is performed in blocks of 2, 4, and 6. No stratifications are applied to the randomization, and the primary investigator is blinded regarding the permuted blocking strategy. A data manager, with no clinical involvement in the trial, prepares the randomization sequence. The allocation is concealed in a password-protected computer file that is only accessible to relevant personnel.

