### Sample size calculation and statistical procedures

To our knowledge, there are no anchor-based minimum clinically important differences (MCID) specifically for physical activity in knee patients. As a substitute, we use an MCID for steps per day, derived from chronic obstructive pulmonary disease research, corresponding to a change of approximately 17%–35% [31]. Applying a 17% threshold to total accelerometer counts per day, based on a previous study of TKA patients [9], yields an anticipated between-group difference in change score of 50,500 activity counts per day. This expected difference is further supported by findings from Van der Walt et al. (2018) [25], who demonstrated a 17% increase in daily step count in the feedback group compared to the non-feedback group after six months. To achieve 80% statistical power (β = 0.80) and detect statistically significant differences at a two-tailed α level of 0.05, assuming a standard deviation of 101,000 counts per day before and after the intervention [9] a sample size of 62 participants per group is estimated. To account for potential dropouts, we use a rate of 20% based upon evidence from a systematic review showing that dropout rates in RCTs on physical activity are within this percentage [32]. Consequently, we will include a sample of 150 patients in total. When appropriate, all outcome measures will be checked for Gaussian distribution using QQ-plots and parametric statistical and/or non-parametric analyses.

No a priori sample size calculation is made for the cohort study. However, based on a total sample of approximately 1,400 annual knee replacement procedures for OUH and Vejle hospitals, it is reasonable to expect an inclusion of 200 patients, which is acceptable for the current statistical analysis plan on predictive regression models [30].

The main comparative analyses between groups will be performed using an intention-to-treat analysis. Between-group mean differences and 95% confidence intervals will be estimated with a linear regression model. The patient’s baseline score is entered as a covariate and adjusted for potential baseline differences (age, sex, BMI). In addition to the intention-to-treat analysis, a per-protocol analysis will be conducted on patients adhering to the intervention (using the patient app for 5 out of 7 days in a week or > 70% of the available days.

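### The planned regression leaves out recruiting site and planned operation type (TKA or mUKA), at a modest cost in precision; the list of sites also needs reconciling

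*Protocol article*

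**What the plan says.** **Allocation.** Under Randomization, the protocol article describes web-based 1:1 allocation through REDCap with permuted blocks of three sizes (2, 4 and 6). On stratification it is explicit: "No stratifications are applied to the randomization". Allocation takes place on the day of surgery, once the baseline measurements are done.

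**Model.** Under Sample size calculation and statistical procedures, the arms are compared by linear regression, with intervals at the 95% level. On covariates the section says: "baseline score is entered as a covariate and adjusted for potential baseline differences (age, sex, BMI"). Neither site nor operation type is in that list.

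**Operation type.** Table 1 admits patients listed for a first TKA or mUKA. Under Patient characteristics, the type of arthroplasty is taken from patient journals after randomisation. It is not among the baseline items named there or under Table 2 (age, gender, height and weight or BMI, work type, surgery leg).

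**Sites.** The Abstract (Methods) gives the recruiting hospitals for the 150 patients as "Odense University Hospital, Denmark, Vejle Hospital, Denmark and Herlev/Gentofte Sygehus, Denmark". Participants and settings lists two departments only, one in Odense and the other being "the Department of Orthopedic Surgery, Lillebaelt Hospital, Vejle, Denmark".

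**The concern.** Site and operation are both plausible predictors of activity at 12 weeks: hospitals may differ in patients and rehabilitation, and the two operations may differ in recovery. Blocks on a single unstratified list balance the total numbers per arm, not the numbers within a hospital or an operation. If the model then omits both factors, a chance imbalance in either is left uncorrected, except for the part that baseline counts, age, sex and BMI happen to carry. Any outcome variation that belongs to site or operation also stays in the residual and widens the confidence interval. The planned power has little slack to absorb that.

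The site list is a separate matter. The Discussion bases external validity on the trial being multicentre, so readers need to know which hospitals recruit.

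**Working it through.** **1. The plan's own figure.** Inputs from Sample size calculation and statistical procedures: difference 50,500 counts/day, SD 101,000, two-sided alpha 0.05, power 80%.

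- n per group = 2 × (1.960 + 0.842)² × (101,000 / 50,500)² = 2 × 7.849 × 4 = 62.8, so 63 (64 by the exact t-test). The stated 62 is reproduced to within two patients.
- Power at 62: SE = 101,000 × √(2/62) = 18,140; 50,500 / 18,140 = 2.784; Φ(2.784 − 1.960) = 79.5%.

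**2. Chance imbalance in operation type.** The mUKA share p is not in the documents; 20–40% is assumed. With 75 per arm, the SD of the between-arm difference in share is √(2p(1 − p)/75):

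| p | SD of difference |
|---|---|
| 20% | 6.5 points |
| 30% | 7.5 points |
| 40% | 8.0 points |

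By the hypergeometric distribution, an imbalance of at least 10 points has probability of about 15% at p = 20% and at p = 30%. For at least 15 points it is 2.4% and 3.2%.

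**3. Shift in an unadjusted difference.** Shift = imbalance × procedure effect in SD × 101,000. The effect is not in the documents; 0.2–0.5 SD is assumed.

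- Low end: 0.10 × 0.2 × 101,000 = 2,020, which is 4% of 50,500.
- High end: 0.15 × 0.5 × 101,000 = 7,575, which is 15% of 50,500.

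For scale, the unadjusted SE with 75 per arm is 101,000 × √(2/75) = 16,493, so the high end is 7,575 / 16,493 = 0.46 SE.

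**4. Imbalance within sites.** Site shares are not given. One unstratified list of 150 in blocks of 2, 4 and 6 was simulated for two equal sites, three equal sites, and a 50/35/15 split. The difference in arm size within a site averaged about 4 to 5 patients, with a 95th percentile of 9 to 12.

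**5. Precision.** If a factor splits patients p to 1 − p with a difference of d SD, it adds about p(1 − p)d² to the variance. For operation type this runs from 0.2 × 0.8 × 0.2² = 0.6% to 0.4 × 0.6 × 0.5² = 6%. Power at 62 per group, with the SD reduced to 101,000 × √(1 − R²):

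| Residual variance explained by site and procedure | Power at 62 per group | n per group for 80% |
|---|---|---|
| 0% | 79.5% | 63 |
| 2% | 80.3% | 62 |
| 5% | 81.5% | 60 |
| 10% | 83.5% | 57 |

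The table treats 101,000 as the SD before the two factors are added. That figure comes from TKA patients only. If mixing in mUKA raised it instead, adjustment would recover a similar amount: with 5%, SD = 101,000 / √0.95 = 103,624, SE = 18,611, and power = Φ(50,500/18,611 − 1.960) = 77.4%, against 79.5% after adjustment.

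**6. Sites side by side.** The Abstract names Odense, Vejle and Herlev/Gentofte. Participants and settings names Odense and Vejle. Both are current text, and they do not agree.

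**The case against.** The strongest reply is that nothing here is an error. Unstratified 1:1 allocation in permuted blocks is openly stated and valid. Its chance imbalances are already reflected in the standard error, and recruitment is under way. All of that stands, so no change to the randomisation is asked for.

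Second, step 3 describes an unadjusted difference, which the plan does not use. Whatever part of a site or procedure effect runs through baseline counts, age, sex and BMI is removed by the planned model. This also stands. A reader might take the 15% as the expected distortion of the primary result; it is the upper end of an assumed range, for a simpler analysis than the one planned.

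Third, an analysis plan that is not shown may add covariates. This is a partial answer: the article does not defer the choice but names a covariate set.

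Two further inferences are tempting and not supported:

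- A reader might conclude that the contradictory site list prevents a site term from being fixed in advance. It does not: the model can name recruiting site as a factor without listing the hospitals.
- A reader might assume that planned procedure is already in the trial data. The article shows only that eligible patients are scheduled for one of the two operations, and that the type is recorded after randomisation.

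**Conclusion.** The point holds as a cheap improvement. The regression omits two plausible prognostic factors in a multicentre trial that mixes two operations. A reader might infer bias or a false-positive problem; the documents support neither, because randomisation is sound and the comparison is unbiased on average. What is lost is some protection against chance imbalance and some precision: about two percentage points of power if the factors explain 5% of residual variance, and four if they explain 10%. These sizes rest on assumed values for the mUKA share, the procedure effect and the variance explained, none of which the documents give. The gain could be close to nil if the effects are small or already carried by baseline counts.

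The disagreement between the two site lists needs no assumption. It is a reporting inconsistency to be put right, with no direct effect on the validity of the analysis.

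**What to change.** - Before unblinding, add recruiting site (as a factor) and planned procedure (TKA or mUKA) as fixed covariates in the primary and secondary models, alongside baseline score, age, sex and BMI.
- Define planned procedure from the surgical schedule as it stood before randomisation, not from the operation recorded afterwards in the journals, so that the covariate is a true baseline variable.
- Reconcile the Abstract with Participants and settings, and give one list of recruiting hospitals throughout.

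Cost: a change of wording in the analysis section, one degree of freedom for procedure plus one (two sites) or two (three sites) for site, and one extra field taken from existing scheduling records. The randomisation and the sample size stay as they are. Fixing the covariates now also avoids the challenge that would follow if they were added after results by arm had been seen.
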